### Study procedures

After (written) informed consent is obtained, all participants will complete two brief tests to assess cognitive impairment, and the participant and caregiver will complete the baseline assessment. Subsequently, randomisation takes place to either (1) the Hospital at Home care-intervention, translocation of care from the hospital to a participants’ home or (2) the control group, usual hospital care. All care will be delivered according to hospital protocols, current regulations and guidelines and, if needed, described in the standard operating procedures (SOPs). If no informed consent is given by either the patient or the caregiver, the reasons for non-participation, date of birth, sex of the patient and the relationship between patient and caregiver will be reported.

## Intervention

### Hospital at Home care

Hospital at Home care will be delivered by a multidisciplinary team consisting of a physician, nurse, pharmacist and physiotherapist. Depending on the participants’ needs, other disciplines (eg, a dietician, occupational therapist or social services) can be involved in the Hospital at Home care. The day-to-day care will be provided by the nurse and physician visiting the participant. The Hospital at Home care team works under the responsibility of the medical specialist in the hospital, and 24/7 consultation of the expertise and services of the hospital is part of the protocol.

The participants allocated to Hospital at Home care will receive hospital level care in their own homes. After a stay of one night in the hospital, while the Hospital at Home care arrangements are being made, the participant will be transferred home and receive Hospital at Home care. The Hospital at Home nurse is responsible for the day-to-day care and will be present on arrival of the participant at his/her residence. Hospital at Home care is described in the care protocols including SOPs and could include intravenous therapy (eg, antibiotics, fluid, and/or diuretics), oxygen therapy, and/or nebuliser, indwelling urine catheter or a nasopharyngeal food tube. After the care intake and a period of direct nursing supervision, the participant will receive intermittent nursing visits daily (starting with three times per day), including weekends and public holidays. The Hospital at Home physician will make a home visit every day (excluding weekends). The Hospital at Home physician and nurse will be available for emergency visits. The participant will receive a medical alert device in the house, with a 24/7 connection to an on-call service. Alert instructions will be explained to the participant and caregiver. A physiotherapist will visit the participant at home to evaluate any problems with balance and/or walking and immobility. The Hospital at Home team works under the supervision of the hospital medical specialist. Daily screenings and measurements will be recorded in a Hospital at Home record, which stays with the participant. Diagnostic procedures and therapeutics that cannot wait and are not available at home, such as endoscopy or CT scan, will be arranged through brief visits to the hospital. The participant will be ‘admitted’ to the Hospital at Home care for as long as indicated.

#### Discharge from Hospital at Home care

If the participant recovers to such an extent that hospital level care is no longer needed, the participant will be discharged from the Hospital at Home care programme, similar to the discharge procedure when the participant would receive usual hospital care. Hospital at Home care will end with discharge planning with the participant, family, Hospital at Home physician and nurse. The discharge plan includes follow-up appointments (eg, at the hospital or general practitioner), information on medication, warning signs and symptoms and an ongoing management plan. All hospital-related care equipment will be removed from the participants’ house, and arrangements with home care agencies and/or paramedical staff will be reviewed and adjusted to the current situation.

### Hospital care as usual

Participants allocated to the control arm will be admitted to a hospital ward and receive usual hospital care. After admission and intake on the ward, the participant will receive intermittent visits from the ward nurse multiple times a day. The ward physician will visit once every day (excluding weekends), with extra visits provided if needed. An emergency alert device, through which nurses and physician can be contacted, will be placed next to the bed. A physiotherapist will visit the participant at the ward to address problems with balance and/or walking and immobility. Depending on the participants’ needs, other disciplines (eg, a dietician, occupational therapist or social services) can be involved in the hospital care. The medical record is the hospital record and additional H@H research forms will be added to this record for research purposes. The participant will be admitted to the hospital for as long as indicated.

#### Hospital discharge

If the participant recovers to such an extent that hospital level care is no longer needed, the participant will be discharged from the hospital after discharge planning with the participant, family, physician and nurse. The discharge plan includes follow-up appointments (eg, at the hospital or general practitioner), information on medication, warning signs and symptoms and an ongoing management plan. Arrangements with home care agencies and/or paramedical staff will be reviewed and adjusted to the current situation.

### Follow-up

At 3 and 6 months following randomisation, all participants will be contacted for an interview by telephone^30^ or a face-to-face interview, if needed. The participants will be allowed to receive support with these questions from their relatives or informal caregivers. An interview will require a maximum of 30 min. In case of institutionalisation or mortality, this event will be recorded. Additionally, information on hospital readmission and length of stay will be collected from the hospital administration system and health insurers. Mortality and nursing home placements will be collected from registries from the general practitioner and municipalities.

### Timing of measurements and outcome measures

Data will be collected at baseline at the ED, during admission (in Hospital at Home or hospital), at discharge and at 3 and 6 months following randomisation, plus or minus 2 weeks. An overview of the timing of measurements and outcome measures are shown in table 2.

**Table 2 T2:** Overview of the content and description of outcome measures and timing of measurements

	Description and instrument	Timing of measurements					
		Screening	Baseline	Admission	Discharge	3 months	6 months
Degree of illness based on physiological parameters	Vital signs alarm score; Modified Early Warning Score^48^	R					
Cognitive impairment	4AT test for delirium*, six-item cognitive impairment test for cognitive impairment*^42 49^	R					
Sociodemographics	Date of birth, nationality, household composition, marital status, highest level of education		R				
Health status	Charlson Comorbidity Index*^50^		R				
Identifying at-risk patients	Safety management system patient screening (VMS)^51^		R				
Functional status	Activities of daily living (ADL), modified Katz-ADL index score^52^		R		R	R	R
Health status	EuroQol-5D-5L*^53^		R		R	R	R
(Health-related) quality of life, well-being	Icepop capability measure for Older people (ICECAP-O)*^54^		R		R	R	R
Caregiver burden	Self-rated burden scale*, caregiver strain index*^55 56^		C		C	C	C
Medical consumption	Imta Medical Consumption Questionnaire (imcq)*^57^		P,C			P,C	P,C
Hospitalisation-associated geriatric syndromes	Infections, falls, pressure injuries, in case of delirium; delirium observation scale score (DOSS)^58^ and use of physical or chemical restraints, total days with a urinary catheter			N			
Nutrition	Malnutrition Universal Screening Tool (MUST)^59^		N				
	Food intake, fluid intake			N			
Pain	Numeric Rating Scale-score (NRS) for pain^60^			N			
Health perception	(Rotterdam) symptom checklist*^61^			N			
Immobility	Hierarchical assessment of balance and mobility (HABAM)^62^			Ph			
Satisfaction with care	Client Satisfaction Questionnaire 8 (CSQ-8)*, care evaluation question*^63 64^				P P, C, N, D		
Mortality	Mortality at 30 days, 3 months and 6 months after baseline*				N	R	R
(Re)admission hospital	Length of stay, readmission rate at 30 days, 3 months and 6 months after baseline*				N	R	R

Assessed by: C, caregiver; D, doctor; N, nurse; P, participant; Ph, physiotherapist; R, research nurse.

*All assessments are extra for trial purposes and are not part of the medical treatment.

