#### Feasibility

For the participation rates, the proportion of participants per step will be calculated. The reasons for non-participation and data concerning the characteristics of non-participants will be collected. We consider the participation rate feasible when it is similar to the participation rate as is described in previous RCTs and around 50% of the eligible patients will consent to participate.^28 29^ Quality of care will be measured by collecting data on patient, institutionalisation (eg, to the hospital or nursing home), mortality, activities of daily living functioning, prevalence of hospitalisation-associated geriatric syndromes, the length of stay in the hospital or Hospital at Home care programme and contact with healthcare professionals. The study is considered feasible if the quality of care of Hospital at Home care on these measurements is non-inferior to usual hospital care.

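### No delirium instrument is scheduled for every participant after randomisation, so recorded delirium can differ between home and ward through detection alone

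*Protocol article*

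**What the plan says.** **Instruments and timing.** In the protocol article, Table 2 (Timing of measurements and outcome measures) lists "4AT test for delirium*, six-item cognitive impairment test for cognitive impairment" with a single mark, in the screening column, for the research nurse. Study procedures also places this testing before allocation: after consent "all participants will complete two brief tests to assess cognitive impairment", and randomisation follows. During admission, delirium appears in the row on geriatric syndromes as "in case of delirium; delirium observation scale score (DOSS", recorded by the nurse. Neither instrument is marked at discharge.

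**Contact with staff.** In the home arm, after an initial supervised period, "the participant will receive intermittent nursing visits daily (starting with three times per day". In the control arm, "the participant will receive intermittent visits from the ward nurse multiple times a day"; no number is given. Trial design states that participants, healthcare professionals and research staff are all unblinded.

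**Use of the result.** The Feasibility section includes "prevalence of hospitalisation-associated geriatric syndromes" among the quality-of-care measures and makes the feasibility conclusion depend on Hospital at Home being non-inferior on those measures. Table 1 allows delirium to be the cognitive condition that qualifies a patient for entry.

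**The concern.** A score that is triggered by delirium cannot serve to find delirium. As worded, someone must first recognise or suspect the condition before the DOSS is completed. The in-stay frequency then reflects two things: how often delirium occurs, and how likely staff are to notice it. Delirium fluctuates, so the second depends on when and how often a professional sees the patient. The protocol describes that contact differently for the two arms, and its third objective treats the timing and intensity of contact as something to be measured, so equal contact cannot be taken for granted.

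At stake is one component of the quality-of-care criterion. Delirium is the first hospital-associated syndrome named in the Abstract and in the Background, and a lower incidence of it is among the cited benefits of Hospital at Home. If the two arms detect it with different sensitivity, the compared percentages answer a different question from the intended one. A larger sample would not correct this.

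A second consequence follows from entry with delirium being allowed. Without a uniform measurement after randomisation, delirium that persists from entry and delirium that develops during the stay cannot be cleanly told apart.

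**Working it through.** **1. What is scheduled for everyone after randomisation.** Reading across Table 2: 4AT at screening only; DOSS during admission, conditional; nothing for delirium at discharge, 3 months or 6 months. Other in-stay entries (pain score, food and fluid intake, symptom checklist, balance and mobility) carry no such condition. The conditional wording is thus a stated rule for this item, not a general style of the table.

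**2. Contact by arm.** Nurse: home visits start at three a day; ward visits are several a day, number not stated. Physician: at home, "The Hospital at Home physician will make a home visit every day (excluding weekends"; the ward physician has the same daily pattern. Extra ward visits are made if needed, and emergency visits are available at home. Home participants spend the first night in hospital, then have an initial period of direct nursing supervision, an alert device and an informal caregiver. The patterns differ, but the text does not say by how much.

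**3. The plan's own count.** 1900 × 0.15 = 285 eligible; 285 × 0.50 = 142.5, rounded to 143, which reproduces the stated figure. A 4:1 split gives 143 × 0.8 = 114.4 and 143 × 0.2 = 28.6, about 114 home and 29 ward.

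**4. Effect of unequal detection (illustration).** Recorded prevalence = true prevalence × detection sensitivity. All prevalences and sensitivities here are assumptions; none is in the documents. Let a be the recorded home rate and b the recorded ward rate. The 95% half-width for the difference is 1.96 × √[a(1−a)/114 + b(1−b)/29]. Ward sensitivity is 90%; home sensitivity is 75%, 60% or 45%.

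| True delirium, both arms | Ward recorded | Home recorded (75 / 60 / 45%) | Home minus ward, points | 95% half-width, points |
|---|---|---|---|---|
| 10% | 9% | 7.5 / 6 / 4.5% | −1.5 / −3.0 / −4.5 | 11.5 / 11.3 / 11.1 |
| 20% | 18% | 15 / 12 / 9% | −3.0 / −6.0 / −9.0 | 15.4 / 15.2 / 14.9 |
| 30% | 27% | 22.5 / 18 / 13.5% | −4.5 / −9.0 / −13.5 | 17.9 / 17.6 / 17.3 |

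The middle case (20% true, 60% against 90%) means 114 × 0.06 = 6.8, about 7 home cases unrecorded that ward-level detection would have recorded.

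**5. A real difference can be hidden.** True delirium 30% at home and 20% on the ward, sensitivities 60% and 90%: 0.30 × 0.60 = 18% and 0.20 × 0.90 = 18%, recorded difference 0. With 90% in both arms: 27% − 18% = +9 points.

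**6. The direction can reverse.** True delirium 20% in both arms, home sensitivity 90%, ward 60%: 18% − 12% = +6 points, a spurious disadvantage for home.

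**The case against.** The strongest reply is that Table 2 is a compressed cell in a journal article. The DOSS carries no asterisk, and the footnote reserves asterisks for assessments added for the trial, so the DOSS reads as routine care. Care in both arms follows hospital protocols and SOPs that are not shown, and the Hospital at Home section mentions daily screenings. A routine delirium check may therefore exist. This stands as a caution: a reader might infer that no systematic delirium screening takes place at all, and the documents do not support that. But the article does not say that the daily screenings cover delirium, and it mentions them for the home arm only. Reading the condition as suspected delirium does not help either, because suspicion still depends on contact.

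A reader might also infer that the bias favours Hospital at Home because ward staff are on site throughout. The documents do not support this. Ward nursing is itself described as intermittent, physician rounds are similar, and a caregiver who knows the patient may report changes that ward staff would miss.

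Finally, the trial disclaims any demonstration of effectiveness, its primary aim concerns recruitment, use and acceptability, and the analysis is descriptive. With about 29 controls, the half-widths above exceed the illustrated shifts. All of this lowers the weight of the point. It does not remove it: the Feasibility section still rests a conclusion on non-inferiority for these measures, and imprecision does not cancel bias.

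**Conclusion.** The point holds as a cheap improvement. Table 2 schedules no delirium instrument for all participants after randomisation, so in-stay detection depends on observation by unblinded treating staff whose contact pattern differs by arm. The recorded prevalence that feeds the Feasibility criterion can therefore differ between arms through detection alone.

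Neither size nor direction can be fixed from the documents. Under-detection at home is plausible because nursing there is by scheduled visits. If it occurred, the assumed ranges above give a spurious advantage of 1.5 to 13.5 points; the opposite assumption gives a spurious disadvantage. These figures show what could happen and are not estimates.

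It would also go too far to say that the defect would mislead the sizing of the later RCT. The outcome that the Discussion names for that purpose is time spent at home, not delirium.

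**What to change.** - **Table 2, admission:** remove the condition and schedule the DOSS for all participants in both arms, at the same set times, regardless of suspicion. Use the same information sources in both arms. Do not add a caregiver item in the home arm alone, since that would make detection differ by design.
- **Table 2, discharge:** add a 4AT by the research nurse, who already administers the Katz-ADL, EQ-5D-5L and ICECAP-O at that point. It cannot show delirium that has already resolved, so it supplements the repeated DOSS and does not replace it.
- **Reporting:** use the screening 4AT to separate delirium present at entry from new delirium, and report the two separately by arm.
- **If uniform daily delirium screening is already part of the care protocols in both arms,** say so in Table 2 and name the instrument and times.

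This changes measurement only, not care. It costs a few minutes of recording per participant per day at existing contacts and one brief test at an existing assessment. Scoring would remain unblinded, so some risk of observer bias stays and should be acknowledged.

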#### Feasibility

For the participation rates, the proportion of participants per step will be calculated. The reasons for non-participation and data concerning the characteristics of non-participants will be collected. We consider the participation rate feasible when it is similar to the participation rate as is described in previous RCTs and around 50% of the eligible patients will consent to participate.^28 29^ Quality of care will be measured by collecting data on patient, institutionalisation (eg, to the hospital or nursing home), mortality, activities of daily living functioning, prevalence of hospitalisation-associated geriatric syndromes, the length of stay in the hospital or Hospital at Home care programme and contact with healthcare professionals. The study is considered feasible if the quality of care of Hospital at Home care on these measurements is non-inferior to usual hospital care.

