**Trial registration number:**

NTR6581; Pre-results.

Strengths and limitations of this studyThis study addresses the feasibility of Hospital at Home care in patients with cognitive impairment, a patient population that is often excluded from participation in scientific research.A process evaluation facilitates the investigation of factors that influence the experiences and perceptions of all persons involved in Hospital at Home care.Stakeholders were involved in the development of the design of the study which will support the implementation of Hospital at Home care and a future trial.Because of a limited sample size due to the study being centred on feasibility, results will not show effectiveness of Hospital at Home care compared with usual hospital care.

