## Methods and analysis

### Trial design

The design is a randomised controlled feasibility trial and will use a process evaluation. This study will be conducted at the medical emergency department (ED) of the academic hospital of the University Medical Center of Groningen in the Netherlands and will evaluate cognitively impaired older patients who are in need of acute hospital care. Figure 1 shows the trial design summary. Participants will be randomised to either Hospital at Home care or usual hospital care in a 4:1 ratio, respectively. Patients will be randomised using a computerised random number generator (http://www.randomization.com), including block randomisation.

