### Sample size of study population

Based on the numbers available from the ED of the University Medical Center Groningen, the Netherlands, we calculated that an average of 3990 older patients 65 years and over is admitted to our medical ED each year. The Hospital at Home trial will be introduced during working hours, which provides an estimated 1900 patients per year. Not all 1900 patients will be eligible for study inclusion. Based on screening of ED medical records, approximately 15% of the patients meet the eligibility criteria for Hospital at Home care, resulting in 285 eligible persons per year. In recent randomised controlled trials (RCTs) of Hospital at Home care in Italy, 54% and 57% of the eligible patients was willing to participate and gave informed consent.^28 29^ We presume a similar consent rate of 50%, as described in these previous clinical trials, and expect for 143 patients to be included.

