### Statistical analysis

The participant flow diagram, according to Consolidated Standards of Reporting Trials (CONSORT) guidelines,^36^ will provide a summary of the recruitment and declination rates in percentage (%) at baseline, discharge and 3-month and 6-month follow-ups. Distributions of the data at baseline, discharge and 3 and 6 months after randomisation will be explored, with unusual values noted and explained. Variables will be summarised as the n (%), mean (SD) or median (IQR) for each group to characterise the sample and search for any imbalances. The percentages, means and SD, and medians and IQRs will be calculated to describe the quality of care and the advantages and disadvantages of Hospital at Home care at baseline, discharge and 3-month and 6-month follow-ups.

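### The feasibility criterion asks for a non-inferiority verdict on quality of care that about 114 versus 29 patients, described by summaries, cannot support unless the margins are very wide

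*Protocol article*

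**What the plan says.** The Feasibility section of the protocol article gives two criteria. The first is participation: the rate is acceptable if "around 50% of the eligible patients will consent to participate". The second is comparative: "The study is considered feasible if the quality of care of Hospital at Home care on these measurements is non-inferior to usual hospital care". The measurements meant include "mortality, activities of daily living functioning, prevalence of hospitalisation-associated geriatric syndromes, the length of stay in the hospital or Hospital at Home care programme"; the list also names institutionalisation and the contacts that patients have with professionals.

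Four other places bear on the second criterion.

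- Trial design: "Participants will be randomised to either Hospital at Home care or usual hospital care in a 4:1 ratio".
- Sample size of study population: from yearly patient flow, an eligible share and a consent rate, the investigators "expect for 143 patients to be included". No margin, error rate or precision target enters this figure.
- Statistical analysis: "The percentages, means and SD, and medians and IQRs will be calculated to describe the quality of care".
- Strengths and limitations (the summary list after the abstract): because the sample is limited, "results will not show effectiveness of Hospital at Home care compared with usual hospital care".

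**The concern.** Non-inferiority is a comparative conclusion. It needs an interval for the difference between arms that is narrow enough to exclude a stated amount of harm. The Feasibility section lets that conclusion support the study's headline result, yet the sample size was not chosen to give such an interval, the allocation makes the control arm small, and the planned analysis is descriptive.

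The error could go either way. If the criterion is applied as a real non-inferiority test with an ordinary margin, the study would probably fail it even when the two forms of care are equally good. If it is applied loosely, so that the absence of a significant difference counts as non-inferior, a sizeable deterioration could pass. The Discussion presents this study as the groundwork for a future randomised trial, so a false stop or a false reassurance would carry forward.

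**Working it through.** **1. The plan's own figure.** Inputs from the Sample size section: 1900 patients per year in working hours, 15% eligible, 50% consenting.

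1900 × 0.15 = 285; 285 × 0.50 = 142.5, which rounds to the stated 143.

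The figure reproduces. It is one year's expected flow. No recruitment period is given in that section, so using 143 as the final sample is an assumption.

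**2. Arm sizes.** At 4:1, 143 × 0.8 = 114.4, so about 114 Hospital at Home and 29 usual care.

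**3. Assumptions, because the document gives no margin or event rates.** Arms truly equal; one-sided 2.5%; event rates p of 10%, 20% and 30%; a 10-point margin for binary measures and 0.5 SD for continuous ones; no dropout.

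**4. Binary measures.** SE = √[p(1−p)(1/114 + 1/29)], where 1/114 + 1/29 = 0.04325. The 95% half-width is 1.96 × SE, power is Φ(margin/SE − 1.96), and the smallest margin with 80% power is (1.96 + 0.84) × SE.

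| Event rate | SE | 95% half-width | Power, 10-point margin | Margin for 80% power |
|---|---|---|---|---|
| 10% | 0.0624 | 12.2 points | 36% | 17.5 points |
| 20% | 0.0832 | 16.3 points | 22% | 23.3 points |
| 30% | 0.0953 | 18.7 points | 18% | 26.7 points |

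Worked line at 20%: SE = √(0.16 × 0.04325) = 0.0832; 0.10/0.0832 − 1.96 = −0.76; Φ(−0.76) = 0.22.

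**5. Continuous measures, in SD units.** SE = √0.04325 = 0.208. Half-width 0.41 SD; power for a 0.5 SD margin Φ(0.5/0.208 − 1.96) = 67%; margin for 80% power 0.58 SD.

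**6. Several measures together.** If all had to pass, take three binary measures (20% rate, 10 points, power 0.224 each) and three continuous ones (0.5 SD, power 0.672 each). With independence the joint probability is 0.224³ × 0.672³ = 0.0034, about 0.3%. By simulation at a correlation of 0.5 it is about 6%.

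**7. The loose reading.** Suppose non-inferior means no significant difference on one measure, and the true rates are 35% with Hospital at Home and 20% with usual care. SE = √(0.35 × 0.65/114 + 0.20 × 0.80/29) = 0.0867. The chance of a significant result is Φ(0.15/0.0867 − 1.96) = Φ(−0.23) = 0.41, so the rise would be missed about 59% of the time.

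**8. Size needed.** For a 10-point margin with 80% power at 4:1, the totals are 445, 785 and 1035 at rates of 10%, 20% and 30%. At 1:1 they are 284, 504 and 660. Changing the ratio alone would not rescue 143 patients at these rates.

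**The case against.** The best defence is that the word is used informally. No margin or test is given, the analysis is descriptive, and effectiveness is disclaimed, so the authors may have meant only that care at home should not look worse. The disclaimer concerns effectiveness and does not mention non-inferiority, so it is in tension with the criterion without directly contradicting it. A margin, error rate or interval could also sit in an analysis plan that is not shown, and its absence from a condensed article is not a fault. These points are fair, but they do not save the criterion: the term has a fixed technical meaning, and a margin written elsewhere would help only if it were very wide.

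Several stronger readings are tempting and go beyond the text.

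- A reader might infer that the study is feasible only if the criterion is met. The sentence says if, and consent is a separate criterion.
- A reader might infer that each listed measure must pass by itself. The sentence can also be read as one overall judgement, so the joint probabilities in step 6 are conditional on the all-must-pass reading.
- A reader might infer that non-inferiority is out of reach at any margin. At a 20% rate, power is 44% for 15 points and 67% for 20 points; at a 5% rate it is 60% for 10 points.
- A reader might infer that length of stay has no worse direction. The Background treats longer stays as a problem in this population. The difficulty is more plausible for contact with professionals.
- A reader might infer that a real harm would generally go unnoticed. The 59% is one scenario on one measure, and a Data Monitoring Committee reviews serious adverse events separately.

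**Conclusion.** The criterion is wrong as written. It ties a feasibility conclusion to a comparative verdict that the stated sample, allocation and descriptive analysis do not deliver. This rests on what the article fixes, and does not depend on details that an analysis plan might supply.

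The size depends on labelled assumptions: 114 versus 29, truly equal arms, one-sided 2.5% and no dropout. For event rates of 10% to 30%, a single binary measure would meet a 10-point margin 18% to 36% of the time. Reliable success would require tolerating differences of about 17 to 27 points, or about 0.58 SD on a continuous measure. At a 20% rate, that means accepting a rise to about 43%. Losses by 3 and 6 months would widen the intervals further; recruitment beyond one year's flow would narrow them.

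**What to change.** Delete the non-inferiority sentence as a feasibility criterion. Report each quality-of-care measure per arm, with the between-arm difference and its 95% confidence interval, and state that no non-inferiority or equivalence conclusion will be drawn. Base the feasibility conclusion on recruitment, use and acceptability, the primary aim set out at the end of the Background. The consent criterion of about 50% already covers recruitment.

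The cost is a wording change in the protocol and in any analysis plan. The sponsor gives up a comparative claim that the design cannot support. No extra patients or data are needed.
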